**Secondary**					
	Unemployment		Unemployed, part-time, or full-time		Nominal
	Unstable housing		Homeless, marginally housed, or housed		Nominal
	Access to health care provider		Multiple items		Nominal and multiple dichotomous items
	Social support		Multidimensional scale of perceived social support		Continuous
	Connectedness to gay community		Items adapted from Healthy Young Men study		Ordinal
	Peer norms for HIV treatment		Perceived peer norms scale		Continuous
	Sociodemographic		Multiple items		Nominal and integer
	Victimization and discrimination		Victimization and discrimination questionnaire		Nominal
	Ethnic identity		Multigroup ethnic identity measure revised		Likert scale, range 1-5

### Measuring and Maximizing Engagement

User data will be measured using metrics such as the number of logins and the amount of time spent on the app, posts created by participants, comments posted, and the messages transmitted between the LINX Coach and participants. Change indicators will also be measured through text message surveys administered weekly, in-person assessment surveys, or via Zoom Video Communications or phone calls at 3 points over the year (baseline assessment, posttest survey at 6 months, and follow-up survey at 12 months after enrollment) and assessments of HIV-related clinical outcomes.

### Statistical Analyses

Statistical methods, models, and procedures will be selected according to the research hypotheses being tested and the types of measures involved. We will set α<.05 as the level for statistical significance but will use appropriate corrections for multiple comparisons (eg, Bonferroni and Hochberg correction) to ensure that the actual overall effective type 1 error remains at a .05 level for the tests to be conducted. The frequency and patterns of missing data were carefully evaluated. To avoid potential bias resulting from missing data, imputation (eg, hot deck or multiple imputation) will be conducted, and statistical significance tests and modeling will be conducted with and without the imputed values. The findings from these analyses will be compared, and any difference will be evaluated. Potential nonlinear relationships between continuous predictors (eg, participants’ age) and outcomes (eg, CD4 count, viral load) will be evaluated through spline functions (eg, cubic spline) [22].

### Planned Analytic Approach

Descriptive statistics of all measures involved (background characteristics, potential moderators and mediators, and outcomes) will be calculated to inform the bivariate analyses and subsequent statistical modeling. On the basis of the nature of the key outcome measures (continuous, categorical, or binary), we will use a full spectrum of analytical approaches to evaluate the data including analysis of variance, analysis of covariance, linear regression, and logistic (binary or ordinal) regression. With 3 time points, repeated-measures missed effect models will also be applied to model the global fixed effect as well as individual participants’ random variation. Our approach to modeling will be to first examine the raw associations with bivariate analyses and then the adjusted and controlled association. Confounding relationships are evaluated through changes in the regression coefficient. The final models will be selected based on goodness-of-fit measures, such as r-square, likelihood ratio, c-statistics, and analysis of covariance, a penalized likelihood. Estimates of effect will be presented with associated 95% confidence limits and associated *P* values.

Preliminary analyses will describe associations between potential predictor variables between both arms of the randomized controlled trial. The initial focus will be to understand the associations between predictors and specified outcomes and to identify confounding or co-linearity that may impact later analyses. We will also describe correlations across various domains to inform the development of our final comprehensive model. We will develop base models predicting engagement in HIV care from demographic predictors (ie, age, education, income, housing status) to identify demographic variables that will be controlled for (as confounding variables or effect modifiers) when examining associations between intervention effects and outcomes. Analyses will be performed to determine robustness and to understand potential confounding or collinearity between predictors. Testing of significance for independent variables will include Wald chi-square tests for continuous or dichotomous variables and/or global goodness-of-fit tests if polytomous categorical variables are regressed. Estimates of effect will be presented with associated 95% confidence limits and associated *P* values.

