### Secondary Outcomes

The overarching framework that informs the study is a social determinant of health model, where we recognize that structural factors (eg, housing instability and poverty) are upstream factors influencing individual-level health behaviors. The information, motivation, and behavioral skills model is the mechanistic model of behavior change. We posit that in the short term, the LINX App will serve to increase participants’ HIV knowledge and help create connections among the participants and connections to existing community-based resources. This may impact both treatment adherence and address issues related to social isolation and stigma. For participants in the LINX App Plus arm of the study, we hypothesize that by offering social and legal services case management, the study could address 2 primary issues facing many in the target population—housing and financial instability.

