### Sample Size Calculation and Power Analysis

Our proposed sample size is based on a comparison of the main outcome of linkage to HIV care between the study arms of the LINX App and LINX App Plus conditions based on a priori logistic regression sample size calculations in PASS 2008 software. Calculations assume linkage-to-care base rates across conditions of 70% based on 2013 estimates of linkage to care within 3 months of an HIV diagnosis for African American people. We also assume a type 1 error of .05 and type 2 error of .2 (or power 80%). Our targeted enrollment of 200 participants in each condition will give us enough power to detect a difference in HIV linkage between LINX App and LINX App Plus arms as low as 12.5%. In addition to comparisons between the 2 study arms as a dichotomous measure, we will also compare linkage to care and other outcomes by intervention dosage as a continuous measure. Comparisons of continuous measures often increase power analyses relative to comparison of dichotomous measures; this comparison is similarly anticipated to do so in our study.

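### The randomized arm comparison is left to coefficient-change and goodness-of-fit model selection, so the primary estimate depends on analyst choice and the precision gain from the baseline outcome is not secured

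*Protocol article*

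**What the plan says.** All the rules are in the protocol article, Planned Analytic Approach. Modelling starts from raw associations and moves to adjusted ones. On the way, "Confounding relationships are evaluated through changes in the regression coefficient", with no size of change given. Then "The final models will be selected based on goodness-of-fit measures, such as r-square, likelihood ratio, c-statistics", followed by a fourth item named as analysis of covariance and described as a penalized likelihood. The criteria are not ranked.

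The control variables come from a separate step: "We will develop base models predicting engagement in HIV care from demographic predictors (ie, age, education, income, housing status"). The variables so identified are to be controlled for, as confounders or effect modifiers, when intervention effects are examined. The rules therefore reach the arm comparison and are not confined to descriptive predictor models.

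The Primary Outcomes section names medication adherence and viral suppression. No section names the baseline value of either as a covariate. The same analytic section does list analysis of covariance, without saying which covariate, and repeated-measures mixed models over three time points, of which baseline is one.

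**The concern.** Confounder hunting belongs to non-randomized comparisons. Here arm is assigned at random, so a baseline covariate can differ between arms only by chance. If the arm coefficient moves when such a covariate enters, the movement reflects that chance imbalance. In logistic regression, which the plan lists, the odds ratio also moves with the covariate set because it is non-collapsible. Neither is evidence of confounding.

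R-square, likelihood ratio and c-statistic measure how well the whole model predicts. They do not say which model gives a valid arm contrast. Screening against engagement in care need not pick the variables that predict adherence or suppression.

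The rules also cannot be executed as written. There is no threshold, no order among criteria, and one item is not a fit measure under the name given (an information criterion was presumably meant). The analyst has to fill these gaps, and may do so after seeing the arm estimates. The corrections in the Statistical Analyses section are for multiple comparisons; they do not mention a search over models within one comparison.

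**Working it through.** **1. The plan's own figure.** Inputs, from Sample Size Calculation and Power Analysis: "Our targeted enrollment of 200 participants in each condition"; "Calculations assume linkage-to-care base rates across conditions of 70" per cent; type 1 error .05; power 80%; able to "detect a difference in HIV linkage between LINX App and LINX App Plus arms as low as 12.5" per cent. Sidedness is not stated; two-sided is assumed. Comparing 70% with 82.5%, the two-proportion formula gives 197 per arm with continuity correction and 181 without, and uncorrected power at 200 per arm is 83.8%. The stated 200 per arm is reproduced within 3%. It concerns linkage to care and does not depend on the point made here.

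**2. Type I error under model choice.** Two separate null simulations, each with n = 400 and four covariates, hence 2^4 = 16 covariate subsets. The 10% threshold is assumed, because the plan gives none.

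| Strategy | Simulation A (2000 runs) | Simulation B (3000 runs) |
|---|---|---|
| Unadjusted | 4.3% | 5.4% |
| Fixed model with baseline outcome | not run | 5.4% |
| 10% change-in-coefficient rule, applied mechanically | 5.1% | 5.5% |
| Best AIC, applied mechanically | 5.1% | 5.8% |
| Most favourable of 16 subsets | 7.7% | 8.9% |

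The Monte Carlo standard error at 5% is √(.05 × .95/2000) = 0.5 points in A and √(.05 × .95/3000) = 0.4 points in B. The first four rows are therefore compatible with a level near 5%. The last row is not.

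**3. Precision from the baseline outcome.** Adjusting for the baseline value multiplies the variance of the arm effect by 1 − r², where r is the baseline-outcome correlation. This holds for a continuous outcome and approximately for a binary one on the risk-difference scale. The documents give no r, so a range is assumed. The equivalent unadjusted total is 400/(1 − r²).

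| r (assumed) | 1 − r² | Equivalent unadjusted total |
|---|---|---|
| .3 | .91 | 400/.91 = 440 |
| .4 | .84 | 400/.84 = 476 |
| .5 | .75 | 400/.75 = 533 |

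In simulation B (r = .5) the mean standard error of the arm effect was 0.100 unadjusted, 0.096 with the best-AIC set of the four covariates, and 0.087 with the baseline outcome. In that setting, selecting among the four covariates recovered only a small part of the gain.

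**4. Does the mixed model already secure this?** Not necessarily. If baseline is a response and the arm-by-time term is free, the contrast behaves like a change score with variance factor 2(1 − r): 1.4, 1.2 and 1.0 at r = .3, .4 and .5, against .91, .84 and .75 above. The gain follows only if the arm means are constrained equal at baseline or baseline enters as a covariate. The text says neither.

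**The case against.** The strongest reply is that a condensed article leaves the exact covariate set to an analysis plan that is not shown, and that the listed analysis of covariance and three-time-point mixed model may well use baseline. That stands. A reader might infer that baseline status is excluded and its precision thrown away, but the documents do not support this. The gain is unsecured; it is not shown to be lost. The reply does not reach the selection rules, which are stated in the text.

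Second, rules applied blindly do no visible harm to the error rate. That also stands. The 8 to 9% requires selecting on the arm P value, which the plan does not propose; the plan also promises robustness analyses.

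Third, engagement in care is not wholly separate from the primary outcomes: Table 1 codes the adherence row to include HIV-related medical appointments, and the sample size section treats linkage to care as the main outcome. This softens the screening criticism. It still leaves viral suppression without a matched covariate set.

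Fourth, part of the recipe is legitimate. The planned analyses by intensity of app use are not randomized and need confounder assessment. The section simply does not separate them from the arm comparison.

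Three further inferences should be resisted. Housing and income are listed controls, and the Secondary Outcomes section hopes that "by offering social and legal services case management, the study could address 2 primary issues facing many in the target population", namely housing and financial instability. Adjusting for follow-up values would remove part of the effect, but the plan calls these variables demographic predictors and nowhere says that follow-up values will be used. An effect modifier would displace the overall arm effect only if an uncentred interaction stayed in the primary model, which is not stated. Finally, a power gain for viral suppression cannot be derived from the documents: pairing the 52% county rate in the Background with the 12.5-point linkage difference would be an invented scenario.

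**Conclusion.** The point holds for the stated rules. A threshold-free, unranked, data-driven selection governs the randomized comparison, so the primary estimate and P value depend on choices that could be made after the arm results are seen. The type I error cost ranges from essentially none, if a rule is fixed and applied mechanically, to about 8 to 9% if the most favourable of 16 covariate subsets is reported. That upper figure depends on the simulated covariates and is not a forecast for this trial.

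The precision part is conditional. If no planned model already uses baseline as a covariate, adjustment would be worth 10% to 33% more participants (440/400 to 533/400) at assumed correlations of .3 to .5. This is a worthwhile correction to the plan; it does not show the trial to be invalid or underpowered.

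**What to change.** Before outcomes are examined by arm, specify one primary model for each primary outcome. It should compare participants by assigned arm and adjust for a fixed set of covariates measured at baseline only: the baseline value of that outcome, plus age, education, income and housing status, kept regardless of fit or of any change in the arm coefficient. If the mixed model is chosen as primary, state how baseline enters it.

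Restrict change-in-coefficient and goodness-of-fit selection to the exploratory predictor models and the non-randomized dosage analyses, and say explicitly that they do not apply to the arm comparison. Report any effect-modifier analysis separately from the main arm effect.

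The cost is analysis-plan wording. Baseline assessments are already part of the design, so no new data or visits are needed.

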### Sample Size Calculation and Power Analysis

Our proposed sample size is based on a comparison of the main outcome of linkage to HIV care between the study arms of the LINX App and LINX App Plus conditions based on a priori logistic regression sample size calculations in PASS 2008 software. Calculations assume linkage-to-care base rates across conditions of 70% based on 2013 estimates of linkage to care within 3 months of an HIV diagnosis for African American people. We also assume a type 1 error of .05 and type 2 error of .2 (or power 80%). Our targeted enrollment of 200 participants in each condition will give us enough power to detect a difference in HIV linkage between LINX App and LINX App Plus arms as low as 12.5%. In addition to comparisons between the 2 study arms as a dichotomous measure, we will also compare linkage to care and other outcomes by intervention dosage as a continuous measure. Comparisons of continuous measures often increase power analyses relative to comparison of dichotomous measures; this comparison is similarly anticipated to do so in our study.

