## Introduction

### Background

African American people accounted for 42% of new HIV diagnoses in the United States in 2018 [1]. Black sexual minority men (BSMM) are further disproportionately affected by HIV. BSMM accounted for 26% of new HIV diagnoses and 37% of new diagnoses solely among all sexual minority men (SMM) in the United States in 2017 [2].

In California, the annual number of HIV diagnoses increased by 0.8% from 2013 to 2017; the rate of HIV infection, however, decreased in California during the same period by 2.4% [3]. In 2017, the number of people living in California diagnosed with HIV was 135,082 individuals [3]. Within this group, 73.6% of these individuals were in HIV care and 63.3% of these individuals achieved viral suppression [3]. African American people living with HIV experienced lower rates of HIV treatment engagement in California compared with White, Latino, Asian, and Pacific Islander people [3].

Los Angeles County (LAC) carries a substantial burden on the HIV epidemic in California. In 2017, 31.6% of all newly diagnosed HIV infections in California came from LAC. Of all people living with HIV in California, 38.1% are from LAC [3]. Within LAC, African American people represented 25% of new HIV diagnoses in 2016 [4]. Between 2015 and 2016, the rate of HIV diagnoses decreased for White people in LAC; however, for African American people, the rate of HIV diagnoses increased during the same period [5]. Approximately 84% of all LAC HIV diagnoses in 2016 were among the SMM. Among those newly diagnosed SMM, linkage to and retention in HIV care was less common among African American people than among White, Latino, or Asian and Pacific Islander people [5].

Data on the continuum of care for people living with HIV in LAC in 2016 revealed that 52% of African American people were linked to care, 65% were engaged in care, 49% were retained in care, and 52% achieved viral suppression [5]. These figures, when compared with people living with HIV across California, indicate that LAC’s African American people living with HIV fare worse in terms of HIV outcomes as they have been proportionately less likely to be engaged in care and to achieve viral suppression [3].

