## Methods

### Overview

The proposed study is a randomized comparison trial of a web-based mobile app titled *LINX*. Participants will be randomly assigned to either the intervention (ie, treatment group) or the comparison group. Those in the intervention group will receive the app and access to a LINX Coach (*LINX App Plus* condition) and those in the comparison group will receive the LINX Mobile app only (*LINX App* condition). Participants in both arms of the study will remain on the mobile app for 12 months. The overarching goal of the study is to evaluate the efficacy of LINX App Plus compared with LINX App to improve HIV treatment outcomes (ie, ART adherence, viral suppression). The research team did not register this study at ClinicalTrials.gov because it did not involve randomization to a true control group. Owing to ethical concerns about withholding the mHealth intervention, all participants received the app; half were randomized to receive coaching.

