### Target Population

The goal of the study is to recruit a minimum of 400 participants for the study. Half of the sampling group (200 individuals) will be randomly assigned to the LINX App condition and the other half will be assigned to the LINX App Plus condition (Figure 1). To be eligible for the study, participants must be aged at least 18 years old or older and must be male, Black or African American, and gay, bisexual, or other sexual minority. Participants must also own a smartphone, be living with HIV, reside in LAC, and be able to provide informed consent.

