### Primary Outcomes

The primary outcomes that the study will measure include the degree to which using the LINX App may impact medication adherence and viral suppression. These primary outcomes were assessed through self-reported data verified through an independent medical chart review. The study will measure how outcomes differ between the LINX App and LINX App Plus conditions and whether the intensity of use of the platform (ie, intervention dosage) is associated with these outcomes.

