**Primary**					
	Technology use		Multiple items		Likert scale, range 1-5
	Medication adherence		Self-reported medication adherence; HIV medical record data		Dichotomous; Yes or No HIV medication adherence or HIV-associated medical appointment
	Viral supression		Viral load and CD4 counts		Continuous

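### The only power statement is for linkage to HIV care, which is not a declared primary outcome; none is given for viral suppression or medication adherence.

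*Protocol article*

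**What the plan says.** The section Sample Size Calculation and Power Analysis opens with this sentence: "Our proposed sample size is based on a comparison of the main outcome of linkage to HIV care between the study arms". The input is given as "Calculations assume linkage-to-care base rates across conditions of 70" per cent, taken from 2013 estimates for African American people of linkage in the first 3 months after diagnosis. With type 1 error .05, 80% power and 200 per arm, the stated detectable difference is 12.5 points in linkage.

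The section Primary Outcomes opens with a different statement: "The primary outcomes that the study will measure include the degree to which using the LINX App may impact medication adherence and viral suppression". Methods, Overview gives the goal as to "evaluate the efficacy of LINX App Plus compared with LINX App to improve HIV treatment outcomes (ie, ART adherence, viral suppression"), and the Objective in the Abstract names the same two outcomes.

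Table 1 lists technology use, medication adherence and viral suppression as primary. Viral suppression is measured by "Viral load and CD4 counts" and typed as continuous. Linkage is not a row. The nearest items are a yes/no element on HIV medical appointments inside the adherence row, and access to a health care provider among the secondary outcomes.

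The section Target Population sets this condition: "Participants must also own a smartphone, be living with HIV, reside in LAC, and be able to provide informed consent". There is no criterion for recent diagnosis or for being out of care.

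Statistical Analyses promises a multiplicity correction, with Bonferroni and Hochberg as examples, to hold the overall type 1 error at .05.

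**The concern.** The article names two different main outcomes. The sample size section powers one of them, and every other section that states an objective or a primary outcome names the others. A reader who meets 80% power for 12.5 points will naturally attach it to viral suppression or adherence, because those are what the trial says it tests. The article gives no rate, standard deviation or effect size for either.

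The input also fits the enrolled population poorly. Linkage in the first 3 months after diagnosis happens once. For a man diagnosed more than about 3 months before enrolment, it has or has not occurred before he is randomised, and coaching cannot alter it.

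At stake is how the result is read: the stated precision does not belong to the outcomes on which the trial will be judged.

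**Working it through.** **Inputs.** From Sample Size Calculation and Power Analysis: 200 per arm, alpha .05, power 80%, base rate 70%, difference 12.5 points. Sidedness is not stated; two-sided is assumed. From Introduction, Background: viral suppression of 52% (African American people in the county, 2016) and 63.3% (all people diagnosed with HIV in California, 2017). The plan does not use these two rates for power; here they are assumptions.

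**Formula.** For control rate p1, comparison rate p2, difference d = p2 − p1 and mean rate m = (p1 + p2)/2, let S0 = √[2m(1 − m)] and S1 = √[p1(1 − p1) + p2(1 − p2)]. Then power = Φ[(d√n − z·S0)/S1], and n per arm = [(z·S0 + 0.842·S1)/d]². Here z = 1.960 at two-sided .05 and 2.241 at .025. With n = 200 and d = 0.125, d√n = 1.768.

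**1. The plan's own figure (70% vs 82.5%).**
- m = 0.7625, S0 = 0.602, S1 = 0.595.
- Power = Φ[(1.768 − 1.960 × 0.602)/0.595] = Φ(0.99) = 84%.
- For 80% power, n = 181 per arm, or 197 with continuity correction. A logistic regression formula for a binary covariate gives 362 in total.
- The 200 per arm and 12.5 points therefore reproduce for linkage.

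**2. Suppression as binary, control rate 52% (52% vs 64.5%).**
- m = 0.5825, S0 = 0.697, S1 = 0.692.
- Power at .05 = Φ[(1.768 − 1.960 × 0.697)/0.692] = Φ(0.58) = 72%.
- Power at .025 = Φ[(1.768 − 2.241 × 0.697)/0.692] = Φ(0.30) = 62%.

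**3. Suppression as binary, control rate 63.3% (63.3% vs 75.8%).**
- m = 0.6955, S0 = 0.651, S1 = 0.645.
- Power at .05 = Φ(0.76) = 78%. Power at .025 = Φ(0.48) = 68%.

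**4. Detectable increase at 80% power, 200 per arm** (the power formula solved for d):

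| Assumed control rate | alpha .05 | alpha .025 | Power for 12.5 points (.05 / .025) |
|---|---|---|---|
| 52% | 13.75 points | 15.1 points | 72% / 62% |
| 63.3% | 12.8 points | 14.0 points | 78% / 68% |

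The .025 column splits alpha equally over the two primary outcomes named in the text, as one simple form of the promised correction. All figures assume 200 analysed per arm. Loss to follow-up would widen them: an assumed 10% to 30% loss moves the 52% case at .05 to 14.5 to 16.3 points.

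**5. Adherence.** The article gives no base rate, so no figure specific to adherence can be derived from it.

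**The case against.** The strongest reply is that the calculation is correct and that care engagement is not absent from the trial. Both points are true. The 12.5-point figure reproduces, so this is not an arithmetic error. The adherence row includes HIV medical appointments, access to a provider is secondary, and Planned Analytic Approach models engagement in HIV care. Some of the conflict may be one of naming. But none of these items is linkage in the first 3 months after diagnosis, which is what the 70% measures, and none gives power for suppression or adherence.

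The sample size section also says that comparing outcomes by dosage, as a continuous measure, should increase power. It gives no numbers, and dosage is not the randomised contrast.

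Some stronger readings are tempting but unsupported:

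- *Linkage is already settled for most participants.* The article reports neither time since diagnosis nor linkage status at enrolment, and it does not exclude recently diagnosed men. It also uses the 3-month figure as the source of the base rate without defining the trial's linkage outcome that way.
- *The article's own county linkage rate contradicts the 70%.* Background reports that "52% of African American people were linked to care, 65% were engaged in care, 49% were retained in care, and 52% achieved viral suppression", but this is a 2016 care-continuum figure with no stated time window, against a 2013 estimate over 3 months. Year and definition differ, so it is no clean contradiction.
- *Every rate in Background can serve as a control rate for suppression.* The 49% is retention in care and the 73.6% is being in care. Only 52% and 63.3% are suppression rates.
- *The true endpoint is viral load below 200 c/mL at month 12.* That threshold appears only where the county's care coordination programme is described, and no section makes month 12 the primary time point.
- *The trial is too small.* With a control rate above roughly 66%, 12.5 points would still have 80% power at .05. The enrolled sample's rate is unknown.

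**Conclusion.** The concern holds as an inconsistency of endpoint. The outcome that sizes the trial is not among its declared outcomes, and neither primary outcome named in the text has a power statement. The stated figure is right for linkage and should not be carried over to suppression or adherence.

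The numerical consequence is moderate. For binary suppression with control rates of 52% to 63.3%, the detectable difference is 0.3 to 1.25 points larger than the stated 12.5 at alpha .05, and 1.5 to 2.6 points larger at .025. This rests on a two-sided test, complete data on 200 per arm, and background rates standing in for the control arm. If suppression is analysed as continuous, as Table 1 types it, these figures do not apply, and a standard deviation that the article does not give is needed.

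**What to change.** 1. Reconcile Primary Outcomes, Table 1 and Sample Size Calculation and Power Analysis, so that all three name the same primary outcome or outcomes.
2. State whether viral suppression is binary, with its threshold and time point, or continuous.
3. Restate the detectable difference at the fixed 200 per arm for each declared primary outcome, at the alpha left after the promised correction. If suppression is binary, a suitable statement is: with assumed control rates of 52% to 63.3%, 80% power for about 13.75 to 12.8 points at two-sided .05, or about 15.1 to 14.0 points at .025 each for two primaries.
4. For adherence, state an assumed base rate with a range, marked as an assumption.
5. Stop calling linkage the main outcome, or define it as a secondary outcome among those out of care at baseline.

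The cost is a rewritten paragraph, a consistent outcome table and a slightly less favourable stated figure. No extra participants or data are required.
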